### 3.6 tTIS stimulation paradigm

The tTIS intervention will be delivered using the High-Definition (HD) Interferential Neuromodulation System (IFS) manufactured by Soterix Medical, Inc. (Woodbridge, NJ, United States). The device is designed to deliver two independent alternating currents to the brain at different frequencies. tTIS will be delivered through two pairs of sintered ring HD electrodes (circular external diameter 1.2 cm) placed on the scalp via a 10-10 HD cap and an HD-GEL (Soterix Medical, Inc.), with each electrode pair delivering continuous high-frequency sinusoidal waveforms at frequencies of 1,000 and 1,130 Hz, respectively, resulting in a carrier frequency of 1,065 Hz and a “beat” frequency of 130 Hz. This stimulation paradigm was designed to mimic the frequency used in DBS of the sgACC for TRD (Mayberg et al., 2005; Khairuddin et al., 2020). The current amplitude will be 2 mA per electrode pair, i.e., the injected current will sinusoidally vary between 0 and 2 mA. The stimulation will be delivered for 30 min, which includes 30-s ramp-up and ramp-down periods at the start and end. For sham stimulation, the current will be ramped down to 0 mA directly after ramping up, mimicking the sensations associated with verum stimulation. Based on our prior experience, we expect to see impedances between 1 and 10 kΩ during stimulation, which is tolerated well by participants. If the impedance of any stimulation channel exceeds 25 kΩ, the stimulation device will give a warning, upon which the experimenter will add gel to reduce the impedance (without stopping the stimulation). If any impedance exceeds 50 kΩ, the channel quality indicator will display red, indicating that the impedance is outside of the preferred range. At this time, stimulation will not cease, and the reduced output current will be delivered in relation to the maximum compliance voltage of the stimulator.

### 3.7 Modeling

Computational modeling was performed to find the 4-electrode tTIS configuration that achieves the highest field strengths in the sgACC. Targeting of the sgACC, therefore, is assumed based on finite element simulations, and has not been previously verified experimentally. Following standard methods, volume conduction models were constructed from MRI images of three healthy adult males, and simulations were performed to calculate the electric fields induced in the head models by injecting current through electrodes on the scalp (Rampersad et al., 2019). Such simulations were performed for 146 million different current patterns, each consisting of 4 electrode locations and current amplitude values for each electrode. The stimulation target was defined as the confluence of three white matter tracts (uncinate fasciculus, cingulum, and forceps minor), corresponding to the location of the sgACC in each hemisphere. This area was marked in the images on which the models were based and then integrated into the models. The current pattern that achieved the highest field strength at the “beat” frequency in this target region was then selected for each model, with a Pareto optimization step to reduce fields in off-target areas, *given the primary objective to maximize field strength in the target*. It is not possible to reduce off-target fields further without reducing the target fields (Rampersad et al., 2019). We used the intersection of the optimal configurations of three models to create a symmetric set of four electrodes. This resulted in electrodes placed at the AF7, T7, AF8, and T8 locations of the international 10-10 system. Figure 2 shows the tTIS electric field strength on a sagittal cut through the target region in one of the head models. With 2 mA (peak) current supplied through each electrode pair, the resulting tTIS electric field strength in the target area was 0.60 V/m. Based on prior modeling and experimental studies of tACS (Rampersad et al., 2019), this should be sufficient to obtain neuromodulatory effects. Some areas of the brain receive higher field strengths than the target region. Due to the geometry of the brain and highly conductive cerebrospinal fluid, this cannot be avoided (Rampersad et al., 2019). However, the current paradigm is optimal for the purpose of this clinical trial: within the set of solutions examined, no other current pattern produced higher tTIS field strength in the sgACC than the one proposed. It should be noted that conventional stimulation, such as tACS, would produce much larger off-target fields even with optimization (see Figures 5 and 11 in Rampersad et al., 2019).

**FIGURE 2 F2:**
[figure not shown]
Computational optimization of tTIS electrode placement. The image shows one of three head models for which the tTIS field strength and focality were optimized. The color scale represents the optimized tTIS field strength distribution in the head. The target region (sgACC) is marked with a black circle.

### 3.8 Study procedures

Participants will complete telephone pre-screening and, if eligible, will be invited to the hospital to undergo urine tests for the presence of pregnancy and substance use, which will be screened out. The screening will involve the review of eligibility criteria, demographics information, medical history, psychiatric history, treatment history, confirmation of MDD diagnosis and the presence of moderate-to-severe symptoms, and a review of safety considerations to receive rTIS or undergo an MRI. If all eligibility criteria are met, written informed consent will be obtained, and participants will be randomized into one of the treatment arms (active tTIS vs. sham). All participants will have 13 on-site visits: screening (Visit 0), baseline combined with day 1 of tTIS (Visit 1), days 2–10 of tTIS (Visits 2–10), and two separate follow-up visits after the last day of tTIS during weeks 3 (Visit 11) and 6 (Visit 12). Visits will be completed on weekdays (Monday to Friday) for compliance and convenience. At baseline (Visit 1) and the last day of tTIS (Visit 10), participants will undergo a 60-min MRI session for the assessment of sgACC target engagement; this session includes the acquisition of anatomical, resting-state functional, perfusion, and diffusion scans. At Visits 1, 5, and 10, resting-state and task-based EEG data will be collected for assessment of changes in brain oscillations that tTIS is likely to modulate (Esmaeilpour et al., 2021). Most clinical assessments will be completed at Visits 5 and 10 to reduce participant burden. The primary outcome time point will be Visit 10, corresponding to the time point at which post-treatment MRI and clinical assessments will be completed. Refer to Table 2 for the study schedule, clinical assessments, and study procedures conducted during each visit.

**TABLE 2 T2:** Proposed schedule of assessments and procedures.

	Study period													
	Enrollment	Baseline	Randomized treatment phase										Follow-up period	
			Week 1					Week 2					Week 3	Week 6
Visit	0	1	1	2	3	4	5	6	7	8	9	10	11	12
**Screening**														
Eligibility	X													
Informed consent	X													
DEMO	X													
MINI	X													
ATHF	X													
MADRS	X													
tTIS/MRI safety	X	X										X		
Urine test	X													
EHI	X													
Allocation		X												
**Interventions**														
A – tTIS (30 min)			X	X	X	X	X	X	X	X	X	X		
B – Sham (30 min)			X	X	X	X	X	X	X	X	X	X		
**Assessments**														
HAM-D-17		X					X					X	X	X
QIDS-SR-16		X	X	X	X	X	X	X	X	X	X	X	X	X
AE			X	X	X	X	X	X	X	X	X	X	X	X
GAD-7		X					X					X	X	X
WHO-5		X					X					X	X	X
SDS		X					X					X	X	X
CONMED		X					X					X	X	X
tTIS-E		X					X					X	X	X
BOAGF							X					X	X	X
**Procedures**														
MRI		X										X		
EEG			X				X					X		

AE, Adverse Events Log; ATHF, Antidepressant Treatment History Form; BOAGF, Blinding Outcome Assessor Guess Form; CONMED, concomitant medications record; DEMO, demographics; EEG, electroencephalography; EHI, Edinburgh Handedness Inventory; GAD-7, Generalized Anxiety Disorder 7-Item; HAM-D-17, Hamilton Depression Rating Scale 17-Item; MADRS, Montgomery-Åsberg Depression Rating Scale; MINI, Mini International Neuropsychiatric Interview; MRI, magnetic resonance imaging; tTIS, transcranial temporal interference stimulation; tTIS-E, Transcranial Temporal Interference Stimulation Expectancy and Experience Questionnaire; QIDS-SR-16, 16-Item Quick Inventory of Depressive Symptomatology – Self-Report; SDS, Sheehan Disability Scale; WHO-5, World Health Organization-Five Well-Being Index.

### 3.9 Clinical assessments

An independently trained rater will administer psychometric instruments, which will be used to assess the effect of tTIS on MDD clinical outcomes. Symptoms of depression will be assessed using the HAM-D-17 (Hamilton, 1960) and 16-Item Quick Inventory of Depressive Symptomatology – Self-Report (Rush et al., 2003). Other measures include validated scales of anxiety [Generalized Anxiety Disorder 7-Item (GAD-7)] (Spitzer et al., 2006), quality of life [World Health Organization-Five Well-Being Index (WHO-5)] (Bech et al., 1996, 2003), and functional impairment [Sheehan Disability Scale (SDS)] (Sheehan et al., 1996). Refer to Table 2 for the frequency of administration. Participants’ expectancy and experience with tTIS and the effectiveness of the rater’s blinding will also be evaluated.

### 3.10 Magnetic resonance imaging

At Visits 1 and 10 (baseline vs. post-treatment), participants will undergo a 60-min MRI (Siemens 3.0 T Skyra) session with a structural and functional protocol using a 32-channel head coil. The MRI protocol comprises: (1) a high-resolution T1-weighted anatomical scan acquired using a magnetization-prepared rapid gradient-echo (MP-RAGE) sequence; (2) a series of B_0_ field map scans to correct the images for signal distortion; (3) fMRI images using a whole-brain T2*-weighted BOLD echo-planar imaging series during the awake resting-state in the eyes-open condition and while viewing a fixation cross (Raichle and Snyder, 2007); (4) a whole-brain diffusion-tensor imaging series; and (5) a 3D pseudo-continuous arterial spin labeling (pCASL) scan. Cardiovascular and respiratory data will be monitored throughout the entire session and used to correct for MRI signal distortions.

### 3.11 Electroencephalography

Before, during, and after tTIS session at Visits 1, 5, and 10, participants will undergo a 42-min EEG data collection, which includes: (1) pre-stimulation EEG at rest with eyes open (3 min); (2) pre-treatment EEG during the auditory MMN task (Näätänen et al., 1978) (3 min); (3) concurrent EEG acquisition during tTIS (30 min); (4) post-stimulation EEG at rest with eyes open (3 min); and (5) post-stimulation EEG during the auditory MMN task (3 min). A 32-channel BioSemi ActiveTwo EEG acquisition system (Cortech Solutions Inc., Wilmington, NC, United States) will be used to collect surface EEG measurements. The desired sampling frequency is 4,096 Hz. Each sample will be quantified at 16 bits, and the digital data will be stored in a secured server for further signal analysis of time and spectral domain features. Auditory MMN is an event-related potential that appears in neurophysiological recordings during a sequence of repetitive sounds that is interrupted by an occasional “oddball” sound, which differs from other sounds in duration or frequency (Garrido et al., 2009). The MMN reflects the flow of the current through NMDA receptor-mediated ion channels and could be used as a biomarker to test whether new interventions influence NMDA receptor responsiveness in study participants (Näätänen, 2001; Garrido et al., 2009; Zhou et al., 2013).

### 3.12 Analysis plan

#### 3.12.1 Primary outcomes: target engagement

BOLD activation (power in the 0.015–0.08 Hz frequency range), CBF, seed-based resting-state FC, and anatomical connectivity of the sgACC will be the primary outcome measures to demonstrate sgACC target engagement with a course of tTIS. We hypothesize that we will observe an increase in the BOLD activation and CBF in the sgACC voxels in the tTIS arm but not the sham and an increase in resting-state FC between the sgACC and bilateral dlPFC, vmPFC, and insula in the tTIS arm but not the sham. We also hypothesize that changes in the resting-state FC will be associated with changes in anatomical connectivity between the sgACC and the abovementioned brain regions. Additional exploratory analyses of changes in the whole-brain FC of the sgACC and their association with anatomical connectivity will be performed.

T1-weighted and T2*-weighted images will be preprocessed, with steps including volumetric segmentation and surface extraction, normalization, motion correction, field unwarping, bias field correction, and brain extraction (Esteban et al., 2019). Preprocessing and denoising will be performed using tedana: TE Dependent ANAlysis v.23.0.1 pipeline^1^ (Kundu et al., 2012, 2013; DuPre et al., 2021), which includes slice timing correction, estimation of motion correction, spatial normalization, signal distortion correction, smoothing, and filtering. The left and right sgACC will be identified using the Desikan-Killiany (FreeSurfer) anatomical labeling scheme (Desikan et al., 2006). Pre- vs. post-treatment changes in sgACC time series properties, such as BOLD activity, will be assessed using Wilcoxon signed-rank tests or paired *t*-tests on signal variance at each sgACC voxel. pCASL scans will be used for perfusion detection using the BASIL toolset to conduct simple CBF quantification in the sgACC voxels (Chappell et al., 2009). In addition, seed-based resting-state sgACC FC maps will be computed by calculating Pearson correlation coefficients between the BOLD time series across the rest of the brain, with a focus on bilateral dlPFC, vmPFC, and insula, and the sgACC voxel-averaged seed time series. Using SPM12, 5 mm spherical seeds will be created around the sgACC MNI coordinates, and contrast analysis on the FC will be run using CONN Toolbox v.22a (RRID:SCR_009550, v.22a) (Nieto-Castanon and Whitfield-Gabrieli, 2021). FC-based target engagement will be defined as statistically significant pre- vs. post-treatment changes in these sgACC FC maps, as computed with mass univariate paired *t*-tests.

Regions strongly anatomically connected to sgACC will be identified using diffusion-weighted MRI tractography. For these analyses, raw diffusion-weighted MRI scans will be preprocessed, denoised, and reconstructed using QSIPrep (Cieslak et al., 2021). The preprocessing and denoising steps include conforming image and gradient orientation, head-motion correction, distortion correction, registration, and normalization. White matter tracts can be extracted from the fiber tractography during reconstruction. The cortical terminations of the sgACC-seeded streamlines will define brain regions anatomically connected to the sgACC. We will conduct additional pre- vs. post-stimulation comparisons on those regions specifically in terms of their signal variance and FC patterns, as described above, and with specific interest in the anatomical connectivity between the sgACC and bilateral dlPFC, vmPFC, and insula.

In addition, we will investigate whether these target engagement metrics are associated with clinical outcomes, as quantified by linear regression analyses. Finally, we will compute tTIS electric field models of T1-weighted MRI images to determine *post hoc* the specific pattern of tissue stimulation experienced by each participant. We will test whether these e-field-computed electrical current intensities are correlated with the regional target engagement metrics outlined above using linear regression models.

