### 3.4 Sample size considerations

Based on studies in TES with fMRI, block design, and use of computational iterative neurostimulation (Ghobadi-Azbari et al., 2021), we expect that 30 participants will have adequate power to demonstrate target engagement of the sgACC. The proposed sample size (*n* = 30) is also based on the overall goal of (a) reasonably assessing the feasibility outcomes and (b) estimating the variability of the clinical outcome measures and is consistent with published recommendations for pilot trials designed to estimate standard deviations for larger future randomized controlled trials when the effect size is small-to-medium (Lancaster et al., 2004; Whitehead et al., 2016). As such, based on sample sizes used in pivotal TES studies (Berlim et al., 2013), we expect that 30 participants will be adequate to demonstrate the feasibility, tolerability, safety, and therapeutic effect of tTIS. Moreover, the pilot study will provide effect size estimates to design a definitive efficacy trial.

For this pilot study, to have a 90% power (i.e., being 90% confident that the effect is true and that it is not a type I/II error), the top end of the two-sided 95% confidence intervals will be the maximum confidence of having a true difference between active tTIS and sham arms. If there is no difference between active tTIS and sham arms, then *p* ≥ 0.051 will indicate no difference with a 90% confidence, and if there is a difference, then *p* ≤ 0.05 will indicate the difference with a 90% confidence. To have the medium effect size of *f* = 0.25 for the mixed-model analysis of variance (Cohen, 2013), 30 patients (15 per group) are required to have a 90% power. We anticipate having a 15% dropout rate in the randomized phase of the study due to side effects or lack of adherence to protocol and approximately a 50% response rate in the acute phase of treatment. A sample size of 15 per group will give us precise estimates of variability in the clinical outcome, namely a change in the Hamilton Depression Rating Scale 17-Item (HAM-D-17) (Hamilton, 1960) score over time (Korn et al., 2012; Cohen, 2013), and this sample size is within the recommended total sample sizes for a precise estimate of the standard deviation and correlation for HAM-D-17 scores to use in the future sample size calculation for a definitive larger scale trial (between *n* = 24 and 50) (Julious, 2005; Sim and Lewis, 2012; Billingham et al., 2013).

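### The first-listed primary outcome is tested on untransformed signal variance by either of two tests, with no rule for choosing and no baseline adjustment; one log-scale model would be firmer and may be more powerful

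*Protocol article*

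**What the plan says.** Section 3.12.1 defines the outcome as "BOLD activation (power in the 0.015–0.08 Hz frequency range") and lists it first among four primary measures. The hypothesis is "an increase in the BOLD activation and CBF in the sgACC voxels in the tTIS arm but not the sham".

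The analysis sentence in the same section reads "Pre- vs. post-treatment changes in sgACC time series properties, such as BOLD activity, will be assessed using Wilcoxon signed-rank tests", then "or paired *t*-tests on signal variance at each sgACC voxel". Three things follow from that wording:

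- Two tests are offered for one primary outcome, and nothing says when each applies.
- The tested quantity is variance, with no log or ratio scale and no covariate.
- Both tests are paired pre/post tests, so neither contains a treatment-arm term.

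The preprocessing steps named for the denoising pipeline are "slice timing correction, estimation of motion correction, spatial normalization, signal distortion correction, smoothing, and filtering". Intensity scaling is neither listed nor ruled out. The filter band is not given, so it is not certain that the tested variance is the 0.015–0.08 Hz power named as the outcome.

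Section 3.4 gives no SD, distribution or power for any MRI measure. Its 90% power statement concerns a mixed-model analysis of variance with f = 0.25.

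**The concern.** Variance and spectral power are squared quantities bounded below by zero. They commonly differ between people by a factor, and a treatment effect on them is often closer to a proportional change than to a fixed increment. When that is so, participants with large baseline variance have the largest post-minus-pre differences. With about 15 people per arm, a few of them can dominate a t-test. A signed-rank test on the same differences repairs this only in part.

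Two things are at stake. One is power, in a 30-participant trial where this is the first-listed primary outcome. The other is that a primary analysis should not leave a choice of test open once the data are visible.

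**Working it through.** **Inputs from the article.** 30 participants, 1:1 allocation, so 15 per arm; 15% dropout, so 30 × 0.85 = 25.5, about 13 per arm; two MRI scans per participant (Visits 1 and 10); two-sided 0.05 level.

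**Inputs assumed, because the article gives none.** Between-participant SD of log variance s = 0.1 to 0.8; scan-rescan correlation r = 0.5 or 0.7; true effect 0.8 SD of the log change; one sgACC value per participant per scan.

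**The plan's own power figure.** It does not describe this test. For the group × time interaction, the noncentrality is λ = f²·N·m/(1 − ρ), with m measurements and correlation ρ. With f = 0.25, N = 30, m = 4, ρ = 0.5: λ = 0.0625 × 30 × 4 / 0.5 = 15, power 0.903, which matches 90%. The article states neither m nor ρ. With the two MRI scans (m = 2) and ρ = 0.5: λ = 7.5, power 0.753. So Section 3.4 supplies no power figure to compare with the tests below.

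**Log-normal model.** log(pre) ~ N(0, s²). log(post) = r·log(pre) + √(1 − r²)·e + δ·arm, with e ~ N(0, s²) and δ = 0.8·s·√(2(1 − r)). For s = 0.8 and r = 0.7, δ = 0.8 × 0.8 × √0.6 = 0.496, a ratio of 1.64. Power in %, 15 per arm, 20,000 simulated trials per setting, shown as r = 0.5 / r = 0.7:

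| s | Active vs sham, baseline-adjusted: log | same, untransformed | Within active arm: paired t on log | paired t, untransformed | signed-rank, untransformed |
|---|---|---|---|---|---|
| 0.1 | 66.0 / 62.0 | 65.8 / 61.6 | 82.1 / 81.8 | 81.8 / 81.6 | 79.8 / 79.6 |
| 0.3 | 66.0 / 61.6 | 63.9 / 59.0 | 81.7 / 82.2 | 79.1 / 79.3 | 78.3 / 78.6 |
| 0.5 | 67.0 / 61.5 | 60.6 / 54.1 | 82.1 / 82.4 | 75.3 / 74.8 | 77.4 / 77.0 |
| 0.8 | 66.3 / 61.9 | 51.0 / 45.3 | 82.1 / 82.1 | 64.1 / 62.8 | 74.6 / 73.9 |

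For the adjusted arm comparison and the paired t-test, the loss on the untransformed scale is 0 to 3 points at s = 0.1 to 0.3. At s = 0.8 it is 15 to 17 points adjusted and 18 to 19 points for the paired t-test. The signed-rank test loses 2 to 4 points at low spread and about 8 at s = 0.8. With 13 per arm the adjusted loss is about 0 points at s = 0.1 and 15 at s = 0.8.

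**Additive normal model.** With baseline mean 1, CV 0.1 to 0.3, the same standardised effect and 15 per arm, the adjusted log analysis has 57.5% to 67.1% power against 61.0% to 67.7% untransformed. The log scale costs between 0.2 and 4.4 points.

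**Two-test choice.** With no effect, taking the smaller of the two p-values rejects in 5.4% to 5.9% of trials across all log-normal settings.

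**Session gain.** If image intensity changed by 5% between sessions, variance would change by 1.05² = 1.10. A gain CV of g adds SD 2√2·g to the log change: 0.141 at 5% and 0.283 at 10%. Against an assumed log-change SD of 0.45 this adds 0.02/0.2025 = 10% to 0.08/0.2025 = 40% to its variance. A log ratio does not remove this; dividing each series by its session mean does, for a purely multiplicative gain.

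**The case against.** Four objections carry weight.

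*Transformation and choice of test are commonly left to an analysis plan, which is not shown.* This would answer a protocol that was silent. Here the article names the quantity and both tests for a primary outcome, so the open choice is in the text. It may reflect the convention of a t-test if differences look normal and a rank test otherwise, but the article does not say so. The absence of a stated transformation, taken alone, would be a weak point.

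*The log-normal model makes the log scale right by construction.* This stands. The article gives no distribution, and under additive effects the log scale loses a little. Even with log-normal data the log scale does not always win: for unadjusted changes between arms, with between-person log-SD 0.1, within-person log-SD 0.2 and an effect of 1.0 SD, the untransformed t-test had power 0.80 against 0.76.

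*A reader might infer that the data are analysed in arbitrary scanner units.* The article does not support that. It never calls the variance raw or unscaled, and its preprocessing lists are not presented as exhaustive. The gain arithmetic is therefore a reason to state the scaling, not evidence that it is missing.

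*A reader might infer that two tests allow serious selective reporting.* The inflation is under one percentage point in these settings. The case for one test is good practice more than error control.

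**Conclusion.** The point holds in a limited form. The article fixes the test of a primary outcome loosely: two tests, no rule between them, an untransformed squared quantity as written, and no baseline adjustment. Power may be lost, but the documents cannot show that it is. The loss is negligible if between-participant log-SD is 0.1 to 0.3 and material, about 16 to 19 points, if it is near 0.8. Both figures assume log-normal values, scan-rescan correlation 0.5 to 0.7, 15 per arm and an effect of 0.8 SD of the log change.

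The trade-off favours the log scale, since its cost under additive effects is at most about 4 points here. It would be too strong to say that the plan loses power as written. It would also be wrong to treat a paired log-ratio test as the remedy: the hypothesis is about active against sham, and no within-arm test answers it on any scale.

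**What to change.** Name one primary analysis for this outcome:

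- Express each voxel series as percent of its session mean.
- Take band power over 0.015–0.08 Hz, average it over the sgACC, and take the natural log.
- Fit a linear model of post-treatment log power with treatment arm as the tested term and baseline log power as covariate.
- Report the active/sham ratio with its 95% CI.
- Remove the either/or wording and keep one rank test as a named sensitivity analysis.

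This also ties the tested quantity to the defined outcome and supplies the sham comparison that the hypothesis needs.

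Cost: no new data and no change to visits or scans. The effect is read as a ratio, one regional value replaces the voxelwise tests as the primary result, and a little power is lost if effects are truly additive.
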